### Study outcomes

Participants will start the protocol as soon as they are fitted with the prosthesis and they are able to walk (approximately 0-3-months post-amputation). The independent variable of this study is the time course (12-months) with measurements taken every 3-months for 12-months (5 visits in total). The biomechanical and psycho-social variables reported in Table 2 represent the dependent variables. Preliminary pilot tests have been performed in the clinical setting on able-bodied participants.

**Table 2 pone.0314523.t002:** Full list of biomechanical and psycho-social variables for analysis.

Variables	Outcome measures
Bio-behavioural	Lower-limb and lumbar kinetics (e.g. joint reaction forces)
	Lower-limb kinematics, including lumbopelvic and lower-limb region movement asymmetries (e.g. joint angles)
	Trunk and lower-limb muscle activations and timings
	Body centre of mass position and symmetry indices
	Temporal-spatial characteristics of gait (e.g. stride length, walking speed)
	Lower-limb-length discrepancies
	Pain intensity/location/type
Psycho-social	Pain attention and interference
	Fear of movement
Psycho-social	Physical activity and quality of life scores
	Anxiety and depression
Other	Anthropometric measurements, socket comfort, prosthesis type, presence of blisters

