### Sample size

The sample size of 30 participants was calculated using G*Power software (3.1.9.7). An *a priori* power analysis was performed based on data from a previous study examining lumbar spine kinematics and LBP amongst persons with unilateral LLA [17]. The estimated sample size was calculated to be N = 26 participants (α = 0.05, 1-b = 0.80), with an effect size of 1.03. However, due to possible challenges with recruiting and retaining participants from clinical practice environments, such as people with limb loss, it is important to account for a 10% drop-out rate [66]. Therefore, the recruitment of at least 30 participants in total will be attempted from the NHS Enablement Centres.

It is important to note that the sample size calculation takes into account only the kinematic variables, and not the relationship with the psycho-social variables measured through the online questionnaires. Ideally, a much larger population would be required for powered analysis of the psycho-social variables, however, due to the time constraints and the lack of data, the estimated sample size of N = 30 patients is the most feasible for the project duration.

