### Statistical analysis

All biomechanical data will be processed in MATLAB® R2023a (MathWorks, Inc) and OpenSim and reported as mean ± standard deviation. Statistical analysis will be conducted using IBM SPSS software (Version 26.0. Armonk, NY). Descriptive data obtained from anthropometrics, online questionnaires, and gait parameters will be analysed by descriptive statistical methods. Biomechanical and psycho-social data will be inputted into a random forest algorithm, which will be used as a dimensionality reduction approach to better explain the variance of the LBP data distribution [72]. Thus, this approach will allow us to evaluate how important each factor is influencing the final outcome (i.e. LBP presence). The process of feature selection is a type of exploratory analysis based on the Pearson’s *r* correlation coefficient to estimate correlations between all the variables collected and LBP. The application of random forest analysis in clinical research is considered a key step towards improving patient related health outcomes [73]. Clinical studies in the literature support the use of random forest analysis for classification performance and prediction, for example in the diagnosis of breast cancer using mammography imaging techniques [74]. Generalised linear mixed models will be used to examine the contributions from biomechanical and psycho-social variables to predict the development of LBP. The variables included in the analysis will be selected based on previous studies [17, 26, 47] and the results from the random forest analysis. Generalised linear mixed models will then be created to identify the best predictors to answer research questions two, three, and four, with pain as a ‘yes/no’ binary variable, and a linear mixed effects model will investigate research question one. Significance will be accepted at *p* < 0.05.

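### Predictors picked by their association with low back pain in the study's own data are then tested at p < 0.05 in the same 30 participants, so those p-values are not valid 5% tests

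*Protocol article*

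**What the plan says.** All of this is in the Statistical analysis section of the protocol article unless stated otherwise.

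- Biomechanical and psycho-social data go into a random forest with LBP presence as the outcome. Feature selection is described as exploratory and rests on Pearson's r, used "to estimate correlations between all the variables collected and LBP".
- The link from screen to model is explicit: "The variables included in the analysis will be selected based on previous studies [17, 26, 47] and the results from the random forest analysis".
- Next come generalised linear mixed models with pain as a binary outcome, which are to identify the best predictors for research questions two, three and four. The rule is: "Significance will be accepted at *p* < 0.05". No split sample, validation, resampling of the whole process or multiplicity adjustment is described.
- Study outcomes gives the data structure: "measurements taken every 3-months for 12-months (5 visits in total"), so up to 30 × 5 = 150 person-visits.
- The subsections on the four research questions give every mixed model a participant random effect. Questions one and two list timepoint as the only fixed effect, and question three lists timepoint and pain with function as outcome. Only question four lists biomechanical and psycho-social predictors.
- Sample size concedes that "the sample size calculation takes into account only the kinematic variables, and not the relationship with the psycho-social variables".

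**The concern.** A variable that enters a model because it correlates with LBP in these participants has already passed a test on the same data. Its p-value in the mixed model is calculated as if it had been named in advance, so the 5% error rate no longer applies. The more candidates are screened and the fewer are kept, the further the true rate rises above 5%.

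The predictors found in this way are meant to inform later care management and rehabilitation. A reader of the results could not tell a predictor that passed a proper 5% test from one that was merely the best of many.

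**Working it through.** **The plan's own figure.** Sample size states: "The estimated sample size was calculated to be N = 26 participants (α = 0.05, 1-b = 0.80), with an effect size of 1.03". The test and its sidedness are not given. Assuming two equal independent groups and a one-sided 5% t-test, d = 1.03 needs 13 per group, 26 in total (power 0.818), which matches. A two-sided test would need 16 per group, 32 in total. With 10% dropout, 26 / 0.90 = 28.9, so 29; the plan rounds up to 30. The figure concerns a single kinematic comparison and says nothing about the error rate of the predictor models.

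**Inputs from the article.** 30 participants; 5 visits; binary LBP/pain outcome; screen of all variables against LBP; mixed model with timepoint and a participant random effect; p < 0.05 per test.

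**Assumptions (not in the article).** Number of candidates m = 14 to 100, mainly 20 to 40; number kept k = 1, 3 or 5; intraclass correlation of candidates 0.6; person SD of LBP 1 or 2 on the logit scale; LBP on about half of visits; correlation between candidates 0, 0.3 or 0.5. On m: eight EMG channels and eight questionnaires already make 16 sources, before kinematics, kinetics, spatiotemporal and sit-to-stand variables.

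**Check.** Simulate with every candidate unrelated to LBP, screen the 150 person-visits, enter the top k with timepoint in a random-intercept logistic model, and count Wald p < 0.05.

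Benchmark without selection:
- One predictor fixed beforehand: 5.1%.
- Three fixed beforehand, by the independence formula: 1 − 0.95³ = 14.3% for any; at the simulated rates of 5.3% to 6.8% each, 1 − 0.947³ = 15.1% to 1 − 0.932³ = 19.0%.
- Five fixed beforehand: 1 − 0.95⁵ = 22.6% by formula; 27.2% simulated, 6.0% with Bonferroni over the five.

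With selection on the same data (ranges are over the two person SDs):

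| Screen | m | k | Each retained predictor | At least one |
|---|---|---|---|---|
| Pearson | 20 | 3 | 27% | 59% |
| Pearson | 40 | 3 | 39% | 73% |
| Random forest | 40 | 3 | 34% | 68% |
| Pearson | 20 | 5 | 19–21% | 61–65% |
| Random forest | 20 | 5 | 18–20% | 57–67% |
| Pearson | 40 | 5 | 30–35% | 78–83% |
| Random forest | 40 | 5 | 27–32% | 77–81% |
| Pearson, correlation 0.3 / 0.5 | 40 | 5 | 18% / 13% | 51% / 39% |
| Random forest, correlation 0.3 / 0.5 | 40 | 5 | 23% / 23% | 65% / 65% |

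The single top-ranked of 40 null candidates (Pearson, k = 1) is significant in 57% of studies. The per-predictor column is the cleanest measure of selection bias, because the last column also contains ordinary multiplicity (27% for five predictors with no selection).

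**How much is due to repeated visits?** With m = 40, k = 5 and person SD 2, a pooled Pearson screen gives 78% for any, a screen on person means 65%, a screen on one visit per person 52%, and no selection 27%. Pooling therefore adds 51 points over the benchmark. Person means, which use all the data without counting visits as independent, still add 38 of these. One visit per person adds 25, although it screens on only a fifth of the outcome records.

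**What repairs it?** Bonferroni over only the five retained predictors does not: 13% to 47% for any. A permutation that keeps each participant's five-visit LBP series intact and takes the maximum screen statistic over all candidates gives 4.9% (m = 40) and 5.3% (m = 100).

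**The case against.** The strongest reply is that this is a 30-person observational study that sets out to explore, calls its feature selection exploratory, admits that psycho-social relationships are unpowered, and takes some predictors from the literature. Part of this stands. Variables fixed beforehand from the cited studies carry no same-data selection bias, and the mix of the two sources is not given. The timepoint-only models for questions one and two are untouched. The exposure is chiefly question four with pain as outcome; function was not the screened outcome. But the exploratory label is attached only to feature selection. The models that follow are meant to answer stated research questions at a significance threshold, and an analysis plan that follows the stated rule inherits the flaw.

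Three stronger readings are tempting, and the article does not support them:
- *That the screen treats 150 visits as independent.* Neither a random forest nor Pearson's r has a participant term and none is described, but the article does not say whether the screen uses all visits, one visit or a per-person summary. If visits are pooled, a nominal 5% Pearson screen flags about 10% to 20% of null variables, which makes matters worse.
- *That most selected predictors would be noise.* The simulations assume no true predictor, so they cannot estimate that share. The Introduction reports earlier associations of LBP with, for example, depression and fear avoidance.
- *That chance predictors will usually be declared significant.* For each retained predictor this fails in nearly all settings. For at least one it depends on the unstated number and correlation of candidates: 39% in one correlated setting.

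**Conclusion.** The point holds for predictors chosen from the study's own data: as the plan is written, their mixed-model p-values are not valid 5% tests. If no candidate is truly related to LBP, and with 20 to 40 candidates and three kept, about 27% to 39% of retained predictors would be called significant, against 5% to 7% if pre-specified. With five kept, at least one false predictor appears in roughly 60% to 80% of studies when candidates are largely independent, and in about 40% to 65% when they are correlated (40 candidates). These sizes rest on the assumed number, number kept, correlation and clustering of candidates. The direction does not: the rate exceeded the matching no-selection benchmark in every setting tried. Most of the inflation comes from reusing the data, and any pooling of visits in the screen adds to it.

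**What to change.** Before outcomes are analysed:

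1. Name a small set of predictors from the cited studies and confine significance claims to these, with multiplicity control such as Holm. Without it, three unadjusted predictors still leave about 15% for any false positive.
2. Label data-selected predictors exploratory and make no significance claim for them. Alternatively, judge them by a permutation or bootstrap that repeats selection plus fitting on whole participants, with all visits of a person kept together, and report selection frequency and optimism-corrected performance.
3. State the data layout of the screen (all visits, one visit or a per-person summary) and, if visits are pooled, resample by participant.

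The cost is a few sentences in the analysis plan and modest programming; no new data are needed. The downside is that fewer predictors can be called significant. Splitting the sample is a poor substitute here: screening in 15 people and testing five predictors in the other 15 gives 38% for any false positive unadjusted and 7.4% with Bonferroni, and leaves only half the participants for the test.

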### Psycho-social risk factors for lower back pain amongst persons with lower-limb amputation

Although psycho-social factors do not appear to be predictive of the initial onset of LBP [29], factors such as anxiety, depression, and fear avoidance have been associated with an increased risk of chronic LBP development in both individuals with and without LLA [43, 44]. A national survey amongst persons with LLA found that depression was significantly associated with ‘bothersome’ LBP [19]. Depression is more common amongst persons with LLA compared to the general population [45, 46], therefore depressive moods may present a greater risk for LBP [47].

Persons with LLA who display fear of using the prosthetic limb may develop dysfunctional movement patterns and subsequent LBP [47–49]. Chou and Shekelle [50] reported that higher fear-avoidance scores were associated with worse functional outcomes and a greater risk of LBP development at 3-, 6-, and 12-months. However, due to the small body of literature, the potential contributory role of psycho-social risk factors to LBP development requires further attention [51]. Acute pre-amputation pain may increase the likelihood of individuals displaying post-operative fear of movement behaviour, which in turn may lead to pain chronification, disability, and reduced patient function [52]. Pre-amputation pain has been associated with a greater risk of post-operative pain 3- and 6-months post-amputation, and a greater duration (>1 month) and intensity of pre-amputation pain is a risk factor for chronic pain [53–55].

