### Objectives and hypotheses

To address this gap, the proposed study protocol will explore the bio-behavioural, psychological, and social characteristics of LBP amongst persons with unilateral LLA over a period of 12-months after their amputation. The whole spectrum of LBP will be explored, including both acute and chronic LBP. To date, this has not been explored in the current literature, and is therefore a novelty and strength of the proposed protocol. Specifically, interactions between bio-behavioural factors of movement (i.e. gait characteristics, trunk and lower-limb muscle activations), and the psycho-social aspects of pain and function will be investigated. Here, the term ‘function’ refers to the comprehensive overview of each participant’s everyday interactions and long-term targets, defined by the participant in terms of person-specific activities and goals. Consideration of these variables aim to improve an understanding grounded in patient-specific function, helping to decipher the relationships between the biopsychosocial characteristics of LBP in individuals with LLA. In doing so, this investigation looks to inform tailored care management and rehabilitation processes.

We hypothesise that individuals who display fear avoidance behaviours will have altered joint range of motion, which in turn will influence muscle activation patterns, leading to greater loading on one side and asymmetries between the sound and residual limb, and therefore increase the risk of LBP development.

Hypothesis 1 (HA1): Gait characteristics will change with time post-amputation and will stabilise following a reduction in movement pattern and trunk muscle activation asymmetries.Hypothesis 2 (HA2): Individuals with a greater risk factor pattern of stressors will experience more pain following the amputation.Hypothesis 3 (HA3): Persons with LLA who experience different types of pain will be at a greater risk of reduced functionality over time.Hypothesis 4 (HA4): Greater scores on psycho-social assessment of pain questionnaires, asymmetric gait patterns, greater and asynchronous activation of trunk muscles, and changes in spatiotemporal characteristics of gait, such as slower gait speed, will be associated with altered pain and function.

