### Questionnaires

Participants will complete eight questionnaires, assessing pain and psychological variables (see S2 Table), using the online software Qualtrics. Patients will complete the questionnaires online within 24-hours of each testing session and the principal investigator will provide support via a phone call. Different types of LBP, including both acute and chronic LBP, will be captured from the questionnaires in order to analyse the full spectrum. Additionally, a box for free comments will be included in the questionnaires (see S2 Fig).

These measures have been validated for use amongst the chronic non-malignant pain population and are widely used in clinical settings for the treatment of chronic pain [62]. The Brief Pain Inventory (α > .70), Pain Catastrophising Scale (α = .87), and the TSK (α = .95) are valid and reliable for use with LBP patients [63–65], however reliability has not been assessed amongst persons with LLA.

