#### Research question three

Function will be modelled as the dependent variable, ‘timepoint’ and pain will be the fixed effects of interest, and participants will be defined as a random effect.

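### Pain is coded yes/no in the models for research questions two to four, which cannot grade the amount of pain (HA2) or, with one pain term, separate pain types and their course over time (HA3)

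*Protocol article*

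**What the plan says.** The Statistical analysis section of the protocol article assigns generalised linear mixed models to research questions two, three and four, "with pain as a ‘yes/no’ binary variable". The same section names presence of low back pain (LBP) as the final outcome of the random forest step.

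The hypotheses under Objectives and hypotheses are worded differently:

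- HA2: "Individuals with a greater risk factor pattern of stressors will experience more pain following the amputation".
- HA3: "Persons with LLA who experience different types of pain will be at a greater risk of reduced functionality over time".
- HA4: the listed factors "will be associated with altered pain and function".

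That section also sets out to explore LBP across its full range, acute and chronic. Table 2 lists pain intensity, location and type among the outcome measures. The Questionnaires section says: "Different types of LBP, including both acute and chronic LBP, will be captured from the questionnaires in order to analyse the full spectrum".

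The short model descriptions are:

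- Research question two: pain as dependent variable, with timepoint as the only fixed effect of interest.
- Research question three: function as dependent variable; the article names timepoint first, then "and pain will be the fixed effects of interest, and participants will be defined as a random effect".
- For question four: both pain and function as dependent variables, with timepoint, biomechanical and psycho-social variables as fixed effects.

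**The concern.** The coding of pain is stated, so this is not a detail left to a fuller plan, and it fits two of the hypotheses badly. A yes/no variable records whether pain is there. HA2 asks whether people with more stressors have more of it, and a participant whose pain goes from mild to severe contributes no change. HA3 asks about kinds of pain and about function over follow-up. A single pain term gives one difference in function between visits with and without pain, whatever the kind of pain and at whatever time.

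At stake is whether the reported models answer the hypotheses at all, and how much of the pain information reaches them. The second matters because the Sample size section concedes that 30 participants were sized on kinematic variables only, and that a powered analysis of the psycho-social variables would need far more people.

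**Working it through.** **The plan's own figure.** The Sample size section gives N = 26 (α = 0.05, power 0.80, effect size 1.03). A one-sided two-group t-test reproduces it: 13 per group, power 0.818. Two-sided, the same inputs need 16 per group, N = 32; the article does not state sidedness. Allowing for 10% drop-out, 26 / 0.9 = 28.9, so 29, which the target of 30 covers. This calculation concerns kinematics and has no bearing on how pain is coded. No figure in the article supports the yes/no coding.

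**Hypotheses against models.**

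| Hypothesis | What it needs | What the model section offers |
|---|---|---|
| HA2 | graded pain; stressor terms | yes/no pain; timepoint only |
| HA3 | pain types; change in function by pain | one pain term plus timepoint |
| HA4 | altered pain and function | yes/no pain, or function; predictors listed |

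The HA2 row has two gaps. Besides the coding, the research question two model lists no stressor, so a graded outcome alone would still not test HA2.

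**Information kept by a yes/no outcome.** Inputs are the prevalences of LBP after amputation in the article's background section on prevalence: 20–30% at one month and 60% at two years. I add 50%, where the efficiency peaks. Assumption, not in the article: pain follows an underlying normal score that is cut to give prevalence p. With φ the standard normal density and z_p the cut point, the efficiency relative to analysing the score itself is

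E = φ(z_p)² / [p(1 − p)]

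| p | φ(z_p)² | p(1 − p) | E |
|---|---|---|---|
| 0.20 | 0.0784 | 0.16 | 0.490 |
| 0.30 | 0.1209 | 0.21 | 0.576 |
| 0.50 | 0.1592 | 0.25 | 0.637 |
| 0.60 | 0.1493 | 0.24 | 0.622 |

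So a yes/no outcome keeps about 49–64% of the information, and loses about 36–51%, per observation. Three limits apply:

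- The formula is for a single observation. With up to five visits per person in a mixed model, it does not convert directly into a number of participants.
- It is for pain as an outcome, so it covers research questions two and four. In question three pain is a predictor, and the formula says nothing about it.
- Real pain scores often have many zeros, so the normal score is a convenience.

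**The case against.** The best defence is that the study is about the development of LBP. The Study design section and the overarching hypothesis both say so, and for that a yes/no outcome is natural. The full range of LBP is only to be explored, and questionnaire data will also be summarised descriptively. That stands as a reason to keep a yes/no analysis. It does not meet HA2, which is worded by amount, and description does not test a hypothesis.

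It can also be said that the pain-by-time term, and the stressors for question two, may appear in a fuller plan. The Statistical analysis section does say in general terms that predictors of LBP will be chosen from earlier studies and the random forest. That is fair, and it softens these two parts. The yes/no coding itself is explicit.

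Four stronger readings are tempting, and the article does not support them:

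- **That HA3 cannot be tested.** This is true only of a model with one pain indicator. Type and location are collected, and a separate yes/no variable for each type would be consistent with the coding.
- **That nearly every visit will be a yes.** The 50–90% figure is an annual prevalence among people with amputation. This cohort enters within about three months of amputation, and the 20–30% and 60% figures are closer to it.
- **That the variable cannot tell LBP from residual-limb or phantom-limb pain.** The Statistical analysis section names LBP presence as the final outcome. It leaves unclear which pain is meant in each model.
- **That the coding dilutes a psycho-social effect confined to chronic pain.** The background does begin "Although psycho-social factors do not appear to be predictive of the initial onset of LBP", but the same section reports fear avoidance linked to LBP development at 3, 6 and 12 months.

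**Conclusion.** The point holds as a mismatch between a stated coding and the stated hypotheses. Yes/no presence serves the question of LBP development. It cannot grade pain for HA2. A single pain term in the research question three model cannot separate pain types or show whether function changes differently over time. The loss for questions two and four is about 36–51% of the information per observation at prevalences of 20–60%. That size is illustrative and rests on the assumed normal score; the mismatch does not depend on it. The remedy lies in the models, because the article says the needed pain information is collected.

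**What to change.** - **Questions two and four:** use the collected pain intensity at each visit as the dependent variable, in a linear or ordinal mixed model. Use an LBP-specific score where there is one; nothing shown establishes that Brief Pain Inventory severity is specific to the low back. Keep yes/no LBP presence for the LBP-development question.
- **Question two:** add the risk-factor (stressor) terms, so that HA2 is tested.
- **Question three:** enter separate indicators for LBP, residual-limb pain and phantom-limb pain, with a pain-by-linear-time term.
- **Acute and chronic LBP:** use the classification that the questionnaires already capture; do not build a new rule from consecutive visits.
- State in each model which pain is meant.

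The cost is analysis wording and a few more terms. If each of the three indicators has its own time term, question three has 3 + 3 = 6 pain terms in place of one. In about 30 people that is a real burden, so these analyses should be labelled exploratory. No new data collection is needed.

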### Prevalence of lower back pain amongst persons with lower-limb amputation

LBP is a serious global health problem and is considered the leading cause of disability worldwide, with 11–38% of the general population experiencing LBP over a one-year duration [13–15]. The annual cost of LBP in the United States is approximately $100 billion, with two-thirds attributed to socio-economic factors including reduced productivity [16]. LBP is an important cause of secondary disability amongst persons with LLA [17], with national annual prevalence rates in four countries (United Kingdom, United States, Sweden, and Vietnam) between 50–90% [18–23]. Following amputation, a one-month prevalence rate of 20–30% [24, 25] and a two-year prevalence of 60% [22] have been reported. Approximately 25–50% of individuals with LBP report the condition as ‘bothersome’ and experience difficulties performing activities of daily living (ADL), including ambulating and standing up from a chair [18].

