### Lower back pain characteristics and gait amongst persons with lower-limb amputation

The experience of pain is a complex biopsychosocial problem, however the interplay between biological, psychological, and social stressors, which may play a role in pain development, is poorly characterised amongst both individuals with and without LLA [26, 27]. Persons with LLA often experience different types of pain, including residual limb pain (RLP), phantom limb pain (PLP), joint pain, and LBP, which can limit individuals from achieving ADLs and pursuing meaningful goals. RLP occurs in the remaining part of the amputated limb often attributed to physical peripheral factors (e.g. local wound healing, neuromas, or poor socket fitting). PLP is defined as a sensation relating to a limb or organ which has been amputated [23, 28], involving peripheral and central nervous system adaptations. LBP is defined as pain around the lumbar spine, it can be multidimensional, and is described by pain location, intensity, frequency, and its impact on ADLs [23]. The experience of frequent (daily or weekly) LBP amongst persons with LLA is associated with moderate/severe physical disability and difficulties performing ADLs [18, 21, 22]. Common examinations for LBP diagnosis and monitoring are radiology, validated questionnaires, and functional outcome measures [29].

Although numerous studies have assessed persons with LLA walking ability [30–33], few have investigated the experience of pain as a variable that may affect walking performance and discrepancies exist regarding the influence of pain on gait outcomes. Currently, there are no longitudinal studies investigating when LBP starts and the consequences, and key variables which may be associated with LBP, including psycho-social factors and muscle activations, are rarely reported. Furthermore, the contributory role of gait analysis factors, such as increased ground reaction forces (GRF), joint loads, and greater time spent on the sound limb [4, 34], have been heavily debated [26]. This is due to studies inaccurately reporting pain location and few specified pain frequency, severity, or intensity [26]. Additionally, others used pain questionnaires which have not been validated in the literature [26].

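### Pain enters the models for research questions two to four only as yes/no, so the graded part of HA2, and any severity effect under HA4, is not tested although intensity is collected

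*Protocol article*

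**What the plan says.** The Statistical analysis section assigns generalised linear mixed models to research questions two to four, "with pain as a ‘yes/no’ binary variable". The same section says the random forest will show "how important each factor is influencing the final outcome (i.e. LBP presence"), so presence is the target there too. Under the research-question headings, pain is the response in question two, a predictor of function in question three, and a response together with function in question four. None of these models is stated to use intensity.

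Elsewhere the article treats pain as graded:

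- HA2 (Objectives and hypotheses): "Individuals with a greater risk factor pattern of stressors will experience more pain following the amputation". HA4 refers to altered pain and function.
- Table 2 (Study outcomes), whose entries the text declares to be the dependent variables: "Pain intensity/location/type".
- Introduction, on earlier work in this population: "few specified pain frequency, severity, or intensity".
- Questionnaires: the Brief Pain Inventory is named among the instruments, which are completed around each of the five visits.

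**The concern.** A yes/no variable puts trivial and disabling LBP in one class. The article itself reports that only 25–50% of people with LBP call it bothersome, so by its own figures 50–75% of the yes class would not. Someone whose LBP rises from 2/10 to 8/10 is coded yes at both visits and contributes no change. A risk factor that worsens pain without affecting whether it is present cannot be found by these models.

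At stake is whether HA2, which is worded as a matter of degree, is tested at all, and whether a study of 30 uses the pain data it collects. The Sample size section already concedes that the calculation covers kinematic variables only. This point is about the scale of the pain variable. Which predictors enter each model is a separate matter.

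**Working it through.** **The plan's own figure.** There is none for the pain models. The stated N = 26 is for kinematics. It reproduces as a one-sided two-sample t-test with d = 1.03, α = 0.05 and power 0.80 (13 per group, achieved power 0.818); a two-sided test would need 32. It has no bearing on how pain is coded.

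**Inputs from the article.** Recruitment target 30; drop-out 10%, hence 30 × 0.9 = 27 completers; LBP prevalence after amputation 20–30% at one month, 60% at two years, and 50–90% as an annual rate.

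**Assumptions not in the article.** A normal latent severity, a person-level risk score correlated 0.5 with it, and a single visit.

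**Step 1: upper bound on the information lost.** For prevalence p, the efficiency of a yes/no cut relative to the fully observed latent severity is φ(z_p)² / [p(1 − p)].

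- p = 0.5: 0.3989² / 0.25 = 0.637
- p = 0.9: 0.1755² / 0.09 = 0.342
- Likewise 0.490 at 0.2, 0.576 at 0.3, 0.622 at 0.6 and 0.490 at 0.8

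This overstates what can be recovered, because a 0–10 rating with zeros for people without pain is not the latent severity.

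**Step 2: the realistic comparison.** The score is 0 when LBP is absent and takes ten equally likely levels when it is present. A Spearman test of the score is compared with a point-biserial test of yes/no, two-sided 5%, n = 27.

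| Prevalence at the visit | Power, 0–10 score | Power, yes/no |
|---|---|---|
| 20% | 43% | 44% |
| 30% | 54% | 51% |
| 50% | 63% | 57% |
| 60% | 69% | 56% |
| 80% | 71% | 44% |
| 90% | 73% | 30% |

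Repeat runs agree to within about two percentage points. At 20–30% most scores are zero, so the score adds almost nothing. The gain is about 6 points at 50%, 13 at 60%, 27 at 80% and 43 at 90%.

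**Step 3: is there a ceiling?** Expected number without LBP among 30: 15 at 50%, 12 at 60%, 7.5 at 75%, 3 at 90%. At 90% the chance of three or fewer without LBP is 0.65, and the chance of none is 0.9³⁰ = 0.042. At 20–30%, only 6 to 9 of 30 would have LBP, which is far from a ceiling.

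**Step 4: hypotheses against models.** HA2 is about amount, while the question-two response records presence. Whatever the prevalence, that response carries no information on severity among people who already have pain. In question three pain is on the predictor side, so the coding coarsens a covariate and does not affect the response.

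**The case against.** The strongest defence is that the study aims to explain how LBP develops, and onset is naturally binary. The Statistical analysis section names presence as the final outcome and seeks predictors of development. This stands: yes/no LBP should stay, and the mismatch does not justify demoting it. It is also fair that altered pain in HA4 does not by itself demand a graded scale. The wording of HA2 does.

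A reader might infer that the outcome saturates across the article's 50–90% range. The documents do not support that. The range is given as "national annual prevalence rates in four countries", not as a rate at a three-monthly visit. The same section also gives 20–30% at one month and 60% at two years, and the article does not state the recall window for the yes/no item. A 50% split is the most informative case for a binary outcome.

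A reader might also take the efficiency figure at 90% to mean that 30 people are worth only about 10 (30 × 0.342 = 10.3). That figure compares yes/no with a perfectly observed latent severity at the extreme of the range, and so overstates what a 0–10 rating would recover. Both calculations also use one observation per person, whereas the design has five visits in a mixed model.

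Finally, the supplementary questionnaire table is not shown, so it is unknown whether the existing intensity item refers to the low back.

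**Conclusion.** The concern holds in a limited form. The article makes a stated choice to code pain only as yes/no in the models for research questions two to four. This conflicts with its own outcome list, with HA2 and with its criticism of earlier studies. The graded part of HA2, and any severity effect under HA4, is therefore untested. That conclusion rests on the text alone.

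The loss of power is conditional. It is negligible at a visit prevalence of 20–30%, modest at 50–60% and large only at 80–90%, under the assumed correlation of 0.5 and a single visit. Since prevalence per visit is unknown, no single figure should be quoted as the cost. In research question three the harm is a coarsened predictor, and no outcome ceiling can arise there. The change should be made, but the binary analysis is not wrong for the development question.

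**What to change.** In Statistical analysis and under research questions two and four, keep yes/no LBP for the development question. Add a mixed model of LBP intensity, scored 0 when LBP is absent, either ordinal (cumulative logit) or linear, and name it as the test of HA2 and of severity effects under HA4. It should carry the risk-factor terms that those hypotheses concern. Under research question three, enter pain as a graded predictor of function.

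If the existing intensity item is specific to the low back, the cost is wording and one extra model to report; an ordinal model is slightly harder to present. If it is not, a low-back rating could be added to the online form only for the remaining visits. Recruitment began on 01/09/2023, so completed visits would lack it, and the report should say so.
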